## Abstract

**Background:**

Despite intensive research over the last several decades on prostate cancer, many questions particularly those concerning early diagnosis and the choice of optimal treatment for each individual patient, still remain unanswered. The goal of treating patients with localized prostate cancer is a curative one and includes minimizing adverse effects to preserve an adequate quality of life. Better understanding on how the quality of life is affected depending on the treatment modality would assist patients in deciding which treatment to choose; furthermore, the development of prognostic biomarkers that indicate the future course of the illness is a promising approach with potential and the focus of much attention. These questions can be addressed in the context of a cohort study.

**Methods/Design:**

This is a prospective, multi-center cohort study within the canton of Zurich, Switzerland. We will include patients with newly diagnosed localized prostate cancer independently of treatment finally chosen. We will acquire clinical data including quality of life and lifestyle, prostate tissue specimen as well as further biological samples (blood and urine) before, during and after treatment for setup of a bio-bank. Assessment of these data and samples in the follow up will be done during routine controls. Study duration will be at least ten years. Influence of treatment on morbidity and mortality, including changes in quality of life, will be identified and an evaluation of biomarkers will be performed. Further we intend to set up a bio-bank containing blood and urine samples providing research of various natures around prostate cancer in the future.

**Discussion:**

We presume that this study will provide answers to pertinent questions concerning prognosis and outcomes of men with localised prostate cancer.

## Background

Prostate cancer is the most frequent newly diagnosed malignancy in men in the Western world, and the second leading cancer-related cause of death. In the USA, 219,000 newly diagnosed cases and 27,000 related deaths have been predicted for 2007 [1]. This data is more clearly described by Walsh [2], who noted that approximately 1 of 6 men in the USA were diagnosed with prostate cancer, while 1 of 34 died from the cancer. Prostate cancer incidence rates continue to increase, although at a slower rate than reported in the early 1990s and prior. Nevertheless, given that the population in the developed world is rapidly aging, the percentage of cases of the disease is expected to rise dramatically. Taking this data into account, the medical and socio-economic consequences of prostate cancer are difficult to estimate.

Despite intensive research over the last several decades, many questions, particularly those concerning early diagnosis and the choice of optimal treatment for each individual patient, still remain unanswered. There are two main problems today.

PSA (prostate specific antigen) screening increases the number of patients suspected of cancer due to the high number of false positive results. Subsequent needle biopsies lead to over-diagnosis and lead to the detection of indolent cancers which would not have affected men in their lifetime [3-6]. Two trails are ongoing investigating the potential benefit due to PSA screening, completion is expected within the next five years [7,8]. Already now some authors questioned the clinical value of these studies. They stated that "it is uncertain whether these trials will have sufficient power to address the primary end point of reductions in deaths from cancer, because PSA screening of the control groups may occur outside these studies and definitive treatment with surgery or radiation therapy is not mandated [2]."

The second problem concerns the selection of appropriate treatment. Adequate choice is difficult because the natural course of disease is often unknown and both patient and clinician face the challenging decision whether active treatment is justified. Indeed, some studies showed a reduction in mortality [9-11]. However, identification which of the available treatments is best for an individual patient remains controversial, particularly because quality of life data are only limited available. Trials in this field are currently in progress. The Veterans Affairs Prostate Cancer Intervention vs. Observation (PIVOT) trial compares radical prostatectomy versus observation in 731 men and will complete the follow-up in 2009. The ongoing UK Prostate Testing for Cancer and Treatment Study (ProtecT) will randomize men with prostate cancer to receive radiation, undergo radical prostatectomy, or remain in observation; this trial is nested within a superior PSA screening trial, and study accrual is estimated to be completed in 2008.

The goal in treating patients with localized prostate cancer is a curative one and includes minimizing adverse effects to preserve an adequate quality of life. Better understanding on how the quality of life is affected depending on the treatment modality – surgery, radiation, active surveillance or even a palliative transurethral resection of the prostate (TUR-P) – would be a first, important step by assisting patients in deciding which treatment to choose. An improvement in the knowledge concerning prognosis would be a further, mostly important step. Here, the development of prognostic biomarkers that indicate the future course of the illness is a promising approach with potential and the focus of much attention. A further topic of interest concerning the prognosis of prostate cancer and prostate cancer survivors is the influence of lifestyle factors, such as nutrition and physical activity. Patients cured from cancer die of non-cancer causes at a higher rate than the general population and co-morbid conditions are probably the result of cancer treatment, genetic predisposition and lifestyle factors [12]. Increasing the knowledge concerning these topics could be of precious help in optimizing treatment outcome.

The purpose of this paper is to describe the rationale, the methodology and the design of a new cohort study. With this study we intend to increase the knowledge on optimal and individualized treatments of men with localized prostate cancer. We believe that its findings will contribute to a better quality of recommendations of physicians at the doctor patient encounter. Moreover, our genetics research branch will provide new insights in pathophysiology of prostate cancer and will have the potential to guide further clinical research particularly in prognostic testing.

## Methods/Design

### Study design

This is a prospective, multi-center cohort study with observational character concerning outcome. We will acquire clinical data including quality of life and lifestyle, prostate tissue specimen as well as further biological samples (blood and urine) before, during and after treatment for setup of a bio-bank.

### Study location

We set up this study within the Canton of Zurich, Switzerland. An expansion to a national or even international study is possible and intended.

### Study population

All men with newly diagnosed localized prostate cancer within the participating urological clinics are principally candidates for study participation. Treatment finally chosen is independent of study participation and *vice versa*. Exclusion criteria are unwillingness to sign the informed consent, an expected survival less than 6 month and referral to the participating urological clinics only for treatment due to intricate data and sample collection.

### Study sample size and duration

We performed a sample size calculation for survival endpoints based on the recommendation of Dupont and Plummer [13]. We have set the alpha error at 0.05 and the beta error at 0.2 and assumed a median survival time in the control group of 15 years. We specified a hazard ratio of the control group relative to the experimental group of 1.2, an accrual time during which patients are recruited of ten years and no additional follow-up time after end of recruitment. Since we are interested in various endpoints we chose an extreme ratio of control to experimental patients of 5 to be on the safe side. Based on these assumptions the required sample size is 1545. Given the size of the catchment's area we anticipate to include about two hundred new patients annually which lead to a sufficient number of patients to perform analyses after the end of the recruitment period.

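### The 5:1 ratio does not make the sample size safe for various endpoints, and 1545 does not deliver the stated 80% power even for the one endpoint that was calculated

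*Protocol article*

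**What the plan says.** All of this is in the protocol article, Study sample size and duration, unless noted.

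- The calculation is for survival endpoints (plural, cause not specified) by the Dupont–Plummer method, with alpha 0.05 and beta 0.2. The authors "assumed a median survival time in the control group of 15 years".
- Effect: "We specified a hazard ratio of the control group relative to the experimental group of 1.2".
- Timing: "an accrual time during which patients are recruited of ten years and no additional follow-up time after end of recruitment".
- Ratio: "Since we are interested in various endpoints we chose an extreme ratio of control to experimental patients of 5 to be on the safe side".
- Result: "Based on these assumptions the required sample size is 1545". The section then expects about 200 new patients a year and judges this enough for analysis once recruitment ends. Over ten years that is about 2,000 men.

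The Objectives section lists survival among several outcomes without naming a cause of death. The only guide to cancer mortality is a US population figure in the Background: "approximately 1 of 6 men in the USA were diagnosed with prostate cancer, while 1 of 34 died from the cancer".

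**The concern.** Two things look wrong.

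First, the reason given for the ratio does not follow. The power of a log-rank or Cox comparison depends on the number of events and on how they split between groups. A 5:1 ratio is a cautious choice about the split. It says nothing about the event count, which changes whenever the endpoint changes. Only one event rate was put into the calculation.

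Second, the reassurance assumes that the base calculation is sound. If 1545 is one group's size read as the whole study, the 80% power is missing for the assumed endpoint too, and every rarer endpoint starts from a lower base.

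Treatment and biomarker comparisons on survival may therefore be read as having 80% power for HR 1.2 when they have far less. A null result would then say little, and a significant one would tend to overstate the effect.

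**Working it through.** **Inputs from the sample size section.** Alpha 0.05 (taken as two-sided, which reproduces the figure), power 0.80, control median 15 years, HR 1.2 (so experimental median 15 × 1.2 = 18 years), accrual A = 10 years, no further follow-up, ratio m = 5 controls per experimental patient. Exponential survival, uniform accrual and no loss to follow-up are assumed.

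**Step 1: reproduce 1545.**
Average median = (15 + 18)/2 = 16.5 years; λ = ln 2/16.5.
Event probability p = 1 − (1 − e^(−λA))/(λA) = 0.1835.
n(experimental) = (1.960 + 0.842)² × (1 + 1/m) / [(ln 1.2)² × p] = 7.849 × 1.2 / (0.03324 × 0.1835) = 1544.3, rounded up to **1545**.
This is the experimental group only. Controls: 5 × 1545 = 7,725. Total: 6 × 1545 = **9,270**.
Read as a total, 1545 did not reproduce in any variant tried with no further follow-up (one- or two-sided alpha, power 0.80 or 0.90, HR 1.2 or 1/1.2, ratio 5, 1 or 1/5).

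**Step 2: effect of the ratio.** By the same formula:

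| Ratio | Experimental group | Total |
|---|---|---|
| 1:1 | 2,574 | 5,148 |
| 5:1 | 1,545 | 9,270 |

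The cautious ratio raises the total but lowers the experimental-group figure. When the group figure is read as the total, caution about imbalance looks like a saving.

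**Step 3: power for the plan's own endpoint.**
Events needed (Schoenfeld) = 7.849 / [(5/36) × 0.03324] ≈ 1,700.
Group-specific event probabilities: control 0.199, experimental 0.170; weighted 5:1 = 0.194.
Power = Φ(√(D × 5/36) × ln 1.2 − 1.96). Detectable HR = exp(2.80/√(D × 5/36)), with D the number of events, held fixed.

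| Total men | Events D | Power at HR 1.2 | HR detectable with 80% power |
|---|---|---|---|
| 1,545 | about 300 | 22% | 1.54 |
| 2,000 | about 390 | 27% | 1.46 |

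Using the averaged probability 0.1835 instead gives 21% and 26%. With group-specific probabilities throughout, the required total is 8,747 rather than 9,270. Neither alters the conclusion.

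**Step 4: a rarer endpoint, as an illustration.** The documents give no cause-specific rate for this cohort, so the cancer share of deaths is an assumption, shown as a range, and the 15-year median is read as all-cause for this step only.

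| Assumed share of the 389 deaths | Events in 2,000 men | Power at HR 1.2 | Detectable HR |
|---|---|---|---|
| 10% | 39 | 6% | 3.3 |
| 30% | 117 | 11% | 2.0 |

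Setting the control group's 10-year prostate-cancer death risk directly, from 1% to 20%, gives 4% to 16% power with 2,000 men. No value in either range comes near 80%.

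**The case against.** The strongest reply is that prostate-cancer death is not a named endpoint. The Objectives speak only of survival, and the language about prognosis could equally mean recurrence or progression. The Statistical analysis section specifies no test of cancer death at HR 1.2. This stands, and it is why cancer death appears here only as an example.

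A reader might infer that the 15-year median can only be all-cause survival. The article says median survival time and no more. All-cause is a plausible reading but remains an inference, and another time-to-event outcome is not excluded.

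A reader might also divide 1/34 by 1/6, take about 18% as the cancer share of deaths, and quote a single number of cancer deaths. The documents do not support that. The figure is a US population ratio not restricted to localized disease, whereas this cohort has localized disease and a mean potential follow-up of about five years at the end of a ten-year accrual.

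Two further replies carry some weight. Per-endpoint precision is something a condensed article may leave to a fuller document. The Abstract also gives a duration of at least ten years, so later follow-up could add events. But the article does not merely stay silent: it makes an affirmative claim of safety and gives a required number. Its calculation also counts no follow-up after recruitment and presents the number as enough for analysis at that point.

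**Conclusion.** The concern holds in this form. The 5:1 ratio addresses unequal groups only and cannot support a claim of safety across endpoints. The stated 80% power at HR 1.2 is not delivered even for the assumed endpoint: 1545 is the experimental-group size, the matching total is 9,270, and about 2,000 men give about 27% power and a detectable HR of about 1.46.

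It would be wrong to conclude that the plan is adequate for the 15-year-median endpoint and fails only for cancer death. It falls short for both, and changing the endpoint alone would not repair it.

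Steps 1 to 3 rest on the article's own inputs, a two-sided alpha, and exponential survival with uniform accrual. The 6–11% for prostate-cancer death rests in addition on the assumed 10–30% share. That power is very low is robust; the exact values are not.

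**What to change.** In the sample size section:

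1. Delete the sentence that presents the ratio as a safeguard for several endpoints. If 5:1 is kept, justify it as an allowance for unequal groups.
2. Define the survival endpoint to which the 15-year control median belongs.
3. State 1545 as the experimental-group size, with 7,725 controls, a total of 9,270 and about 1,700 events, and say plainly that expected recruitment is about 2,000.
4. For each survival endpoint of interest, give the expected events and the HR detectable with 80% power at about 2,000 men. Label any cause-specific rate as an assumption and show its range.

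Optionally, endpoints with few expected events could be reported at the end of recruitment as estimates with confidence intervals only.

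The cost is a short table and a few sentences. Recruitment and data collection need not change. The downside is that the stated detectable effects become less favourable: about 1.46 instead of 1.2 for the assumed endpoint, and larger for anything rarer.

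### The required sample size of 1,545 matches the smaller group alone; the total is about 9,270, so the planned 2,000 men give about 26% power for a hazard ratio of 1.2, not 80%

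*Protocol article*

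**What the plan says.** The only sample-size justification is in the protocol article, Methods/Design, Study sample size and duration. Its inputs are:

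- error rates: "We have set the alpha error at 0.05 and the beta error at 0.2" (one- or two-sided is not stated);
- control survival: "assumed a median survival time in the control group of 15 years";
- effect: "We specified a hazard ratio of the control group relative to the experimental group of 1.2";
- accrual: "an accrual time during which patients are recruited of ten years";
- follow-up: "no additional follow-up time after end of recruitment";
- group ratio: "we chose an extreme ratio of control to experimental patients of 5 to be on the safe side".

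The result is "Based on these assumptions the required sample size is 1545", with no indication of whether this counts one group or both. The paragraph then says "we anticipate to include about two hundred new patients annually which lead to a sufficient number of patients" for analysis once recruitment ends. Two hundred a year for ten years is 2,000 men in all, so the text treats 1,545 as the size of the whole cohort.

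**The concern.** A hazard ratio of 1.2 is a small effect, a 5:1 split is inefficient, and a 15-year median with ten years' staggered entry and no further follow-up leaves most men alive at analysis. A total of 1,545 looks far too small for that combination. Sample-size routines for unequal groups often report the size of the experimental group, with the controls to be added as a multiple. If that happened here, the controls were left out.

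The first objective includes survival in relation to treatment modality and prognosis, and the study means to derive treatment recommendations. If the paragraph stands, a non-significant survival comparison could be taken as well-powered evidence of little difference when the design had about a one-in-four chance of detecting the effect it names.

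**Working it through.** **Inputs.** All are from Study sample size and duration: alpha 0.05, power 0.80, control median 15 years, hazard ratio 1.2 control to experimental (so experimental median 15 × 1.2 = 18 years), accrual 10 years, follow-up 0, ratio m = 5. Assumptions added here: two-sided test, exponential survival, uniform accrual, no loss to follow-up.

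**Step 1: probability of death by the analysis.** With uniform entry over 10 years and hazard λ = ln 2 / median,

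p = 1 − (1 − e^(−10λ)) / (10λ).

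| Median (years) | λ per year | p |
|---|---|---|
| 15 (control) | 0.0462 | 0.199 |
| 18 (experimental) | 0.0385 | 0.170 |
| 16.5 (mean of the two) | 0.0420 | 0.1835 |

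**Step 2: reproduce the plan's figure.**

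n(exp) = (z₀.₉₇₅ + z₀.₈₀)² × (1 + 1/m) / [(ln 1.2)² × p]

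= 7.849 × 1.2 / (0.03324 × 0.1835) = 1,544.3, rounded up to **1,545**.

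This is the printed number to the last digit, and it is the number of *experimental* patients. The total is 1,545 + 5 × 1,545 = 1,545 + 7,725 = **9,270**.

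Other choices for the same two-sided problem:

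| Choice | Experimental group | Total |
|---|---|---|
| Schoenfeld, weighted event probability | 1,458 | 8,747 |
| Unpooled variance | 1,626 | 9,754 |
| Freedman | 1,649 | 9,894 |
| p at median 15 | 1,422 | 8,534 |
| p at median 18 | 1,666 | 9,998 |

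No variant tried gives 1,545 as a total. The smallest total at 5:1, with a one-sided test and the hazard ratio reversed, is about 5,800. At 1:1 with the same relaxations it is about 3,450.

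**Step 3: a check that does not depend on where 1,545 came from.** Deaths needed at 5:1:

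d = 7.849 / [(1/6)(5/6)(ln 1.2)²] = 7.849 / (0.1389 × 0.03324) ≈ **1,700**.

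With a two-sided test, 1,545 men could not supply 1,700 deaths even if all of them died. Expected deaths at the end of recruitment, with p at the mean median and then weighted over the groups, are 283 to 300 in 1,545 men and 367 to 389 in 2,000.

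**Step 4: power of the cohort as planned.** Power = Φ(√(N × p × 5/36) × ln 1.2 − 1.96).

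| N (total) | Deaths | Power for 1.2 at 5:1 | Hazard ratio with 80% power at 5:1 |
|---|---|---|---|
| 1,545 | 283–300 | 21–22% | 1.55–1.62 |
| 2,000 | 367–389 | 26–27% | 1.47–1.52 |
| 9,270 | 1,701–1,802 | 80–82% | 1.2 (design value) |

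With an even split, 2,000 men give about 42%.

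**Step 5: the group ratio.** By the formula in Step 2, moving from 1:1 to 5:1 lowers the experimental-group figure from 2,574 to 1,545, while the total rises from 5,148 to 9,270. The 5:1 ratio is cautious only if the total is what gets reported.

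**The case against.** **Sidedness is not stated.** This is true, and the remark that 1,545 men could not supply the deaths even if all died holds only for a two-sided test. One-sided, the requirement is 6.183 / (0.1389 × 0.03324) ≈ 1,339 deaths. But one-sided power is still only 31–32% with 1,545 men and 37–38% with 2,000, and one-sided formulas do not return 1,545 (they give 1,148 to 1,299 per experimental group).

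**The article never says which group 1,545 counts, and the exact match relies on averaging the two medians, a step it does not print.** This is fair: the origin of the number is a strong inference, and the authors should confirm it. The conclusion does not depend on it. If 1,545 was meant as the total, it is too small. If it was meant as the experimental group, 2,000 recruits leave 455 controls where 7,725 are needed. The claim of sufficiency fails either way.

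**Choosing 5:1 as a cautious ratio is sound reasoning about totals.** This stands. The ratio is not itself an error; the fault is that the reported number leaves out the controls the ratio calls for. Why the authors regarded it as safe cannot be known from the text.

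**This is an observational cohort and bio-bank with several objectives, at least ten years' duration and possible expansion, so little hangs on one hazard ratio.** This softens the consequence. Later analysis helps: with 2,000 men at 5:1, power is 42–44% five years after recruitment closes and 54–56% after ten. With an even split, it is about 79% after ten. But the paragraph itself fixes no further follow-up and a 5:1 ratio, and on those terms its figure is wrong.

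**Conclusion.** The concern holds. On the protocol's own inputs, 1,545 is reproduced exactly as the size of the experimental group, and the corresponding total is about 9,270 (8,500 to 10,000 across the two-sided choices shown). That is about 4.6 times the 2,000 men expected. At the planned analysis, power for a hazard ratio of 1.2 is 26–27% with 2,000 men, and 21–22% with 1,545, against the stated 80%. These figures assume a two-sided test, exponential survival, uniform accrual and no loss to follow-up; losses would lower power further. A one-sided test leaves power below 40%. The inputs, result and conclusion are all printed in one paragraph and do not agree, so condensation into an article does not explain the discrepancy.

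**What to change.** Rewrite the paragraph under Study sample size and duration:

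1. Confirm and state that 1,545 is the experimental-group size, with 7,725 controls and 9,270 men in total. State that the test is two-sided and how the event probability was obtained.
2. Withdraw the statement that about 200 men a year is sufficient for a hazard ratio of 1.2.
3. State what about 2,000 men deliver at the end of recruitment: roughly 370 to 390 deaths, 80% power at 5:1 for a hazard ratio of about 1.47 to 1.52, and 26–27% power for 1.2.
4. Optionally, add the power for 1.2 at 5:1 if survival is analysed later in the same cohort: 42–44% five years after the last recruitment and 54–56% after ten.

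The cost is one reworded paragraph and a less favourable detectable effect. Recruitment, procedures and analyses need not change.
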